## Abstract

**Background:**

Physiotherapy in the clinic is highly recommended for improving gait, balance, and fall risk in people with Parkinson’s disease. In addition, technology may help boost unsupervised exercise hours at home. Strolll is an augmented-reality (AR) neurorehabilitation platform for delivering gait-and-balance exercises onto AR glasses that can be performed under direct supervision of the therapist in the clinic, but also independently at home. Strolll AR also has the option to integrate AR cueing in gait-and-balance exercises to assist people with more severe mobility impairments in performing the exercises. The objective of this pragmatic randomized controlled trial (RCT) on Strolll AR is to examine its clinical feasibility and effectiveness for improving indicators of gait, balance, and falls risk. A secondary objective is to evaluate procedures for tailoring assistive AR cues.

**Methods:**

A total of 100 people with Parkinson’s disease (Hoehn and Yahr stages 1–3) with gait and/or balance impairments will participate in this study. This study is a pragmatic RCT in which all participants follow the same procedure. After a baseline assessment (T0), participants will start with a 6-week usual care control period, followed by a midterm assessment (T1). Subsequently, participants will undergo 2 weeks of in-clinic familiarization with Strolll AR. Then, participants will start with the 6-week Strolll AR intervention at home, followed by a final in-clinic assessment (T2). The primary study parameters are feasibility (i.e., safety, adherence, performance, and user experience) and effectiveness for improving indicators of gait, balance, and falls risk. For the statistical analyses on effectiveness, participants will be allocated to control (using T0-T1 change data) or intervention (using T1-T2 change data) groups using multiple (*n* = 20) randomizations. Recruitment started in May 2024 and the last T2 assessment is expected in February 2025.

**Discussion:**

The design of this particular pragmatic RCT will demonstrate feasibility and effectiveness in a real-world setting and in a representative population. Strolll AR may facilitate the transition from supervised care in the clinic to independent care at home, providing a platform for delivering individualized treatment, assisted with AR cues when deemed beneficial, for improving gait, balance, and falls risk in people with Parkinson’s disease.

**Clinical trial registration:**

https://clinicaltrials.gov/, identifier NCT06590987

## Introduction

1

People with Parkinson’s disease face motor symptoms that limit activities of daily life (1–3), restrict participation (1, 2), and elevate falls risk (4). Physiotherapy for people with Parkinson’s disease aims to maximize quality of movement, functional independence, and general fitness, and to minimize secondary complications while supporting self-management and participation, and optimizing safety (5). It addresses core aspects like physical capacity, transfers, posture, upper-limb function, (in)activity utilizing cueing strategies, balance (and falls), and gait (2, 5), with balance and gait impairments often being indicators for an elevated falls risk (4). People with Parkinson’s disease often have a sedentary lifestyle (6), which may further worsen motor symptoms and associated falls risk. Physiotherapy, including prescribed unsupervised exercises at home, is highly recommended for improving gait, balance, and falls risk (1, 2, 7). That is, guidelines specific for people with Parkinson’s disease recommend to exercise for at least 150 minutes per week at a moderate to vigorous intensity, which can include (brisk) walking, balance training, and strength exercises (1, 7, 8), tailored to the specific needs of the person with Parkinson’s disease for the best outcome (9). However, this is often a difficult exercise target to reach and monitoring of the adherence often relies on self-reporting (10).

Emerging technology may help boost unsupervised exercise adherence at home (11). So far, most of these innovations, such as virtual-reality or screen-facing solutions have demonstrated promise in improving patient engagement and mobility outcomes (12–14). However, these technologies primarily focus on immersive or static experiences rather than facilitating interaction with a real-world environment. A promising technology in that regard is Strolll, an augmented-reality (AR) neurorehabilitation platform for delivering gait and balance exercises for Parkinson’s disease onto state-of-the-art AR glasses^1^ like Magic Leap 2 and Microsoft HoloLens 2. Various gamified and structured therapeutic exercises have been co-designed with people with Parkinson’s disease, therapists, and other stakeholders for gait and balance practice, aimed at obtaining engaging, effective therapy at high adherence (15). The Strolll AR platform comprises seven AR exercises that can be performed under direct supervision of the therapist in the clinic (Figure 1A), but also independently by people with Parkinson’s disease at home (Figure 1B), remotely prescribed and tailored by their therapists. Recently, Hardeman et al. (15) examined in a waitlist-controlled trial the feasibility and potential efficacy of Reality DTx^®^, the precursor of Strolll AR, for improving gait, balance, and falls risk in people with Parkinson’s disease in a research setting. This 6-week remotely prescribed home-based AR program was safe, adherable, usable, and well-accepted, with targeted intervention effects for improving indicators of gait, balance, and falls risk (15). Building on these promising results, obtained in a research setting, the current study aims to evaluate the feasibility and effectiveness of Strolll AR implemented in the clinical pathway, where therapists from more than 10 physical or exercise therapy clinics will integrate the Strolll AR platform with usual care, starting supervised in the clinic and then performed independently at home by people with Parkinson’s disease.

**Figure 1 fig1:**
[figure not shown]
**(A)** Example of a Strolll AR gamified gait-and-balance exercise (i.e., Basketballl) performed in the clinic under the supervision of a therapist. **(B)** Example of a Strolll gamified gait-and-balance exercise performed independently at home (i.e., Smash!) complemented with assistive AR cues.

New to the Strolll AR platform is the option to integrate AR cueing in gait-and-balance exercises, which will assist people with more severe mobility impairments, like freezing of gait and festination, in performing the exercises. Cueing in the form of spatial (like visual lines or stepping targets) or temporal (like an acoustic rhythm) external stimuli aids the initiation, facilitation or modification of gait, generally with immediate effect (16–18). The effects of AR cueing delivered on state-of-the-art AR glasses with large vertical AR fields of views like Microsoft HoloLens 2 and Magic Leap 2 is not too dissimilar anymore from traditional cueing options. For example, our previous work showed that AR cueing alleviated freezing of gait in people with long and/or many freezing episodes (19) and that the gait-modifying effects of AR cueing were similar to those of real-world cueing [e.g., in terms of step-length and walking-speed modulation; (20)]. As cueing is not a one-size-fits-all solution (21, 22), the AR cues in the current study will be tailored to the individual’s preferences (e.g., some people benefit from 3D cues to step over, others from 2D cues to step onto (22, 23)) and gait characteristics (e.g., intercue distances fitting a person’s step length and width) in an attempt to yield optimal cueing effects during Strolll AR gait-and-balance exercises.

The objective of this pragmatic randomized controlled trial (RCT) on Strolll AR, an individualized AR gait-and-balance exercise platform complemented with tailored AR cues when deemed beneficial, is to examine its clinical feasibility and effectiveness. We expect that Strolll AR is (i) clinically feasible in terms of safety, adherence, performance, and user experience (i.e., for both people with Parkinson’s disease and their therapists) and (ii) effective for improving indicators of gait, balance, and falls risk in people with Parkinson’s disease. The secondary objective of this study is to evaluate procedures for tailoring assistive AR cues to individuals when deemed beneficial in performing the AR gait-and-balance exercises. We expect that many of the participants, particularly those with more severe mobility impairments like freezing of gait and festination, could benefit from assistive AR cues integrated in the AR exercises and that they use a variety of cue settings, thereby substantiating the necessity to personalize AR cues.

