#### Practice with Strolll AR intervention supervised in clinic (2 weeks)

2.2.5

To make the participant familiar with the Strolll AR platform technology and procedures and to allow the therapist to evaluate safety aspects, the Strolll AR intervention starts with 1 to 3 supervised in-clinic sessions of (cueing-assisted) personalized AR exercises.

In these supervised sessions in the clinic, the therapist will also test and validate procedures to select and tailor effective assistive AR cues from a library of different AR cues (see Supplementary material S2 for the types of cues used in this study). This is needed for two reasons: (1) to test the premise that a one-size-fits-all cue does not exist as there is heterogeneity in the effect of cues among participants, (2) to ensure that the Strolll AR gait-and-balance exercises can be effectively assisted with personalized cues for those who need it (e.g., people experiencing freezing of gait or people with small steps and shuffling gait (16–18)). The so-obtained best cues for supporting gait, as evaluated subjectively using both the participant’s experience and the therapist’s impression, will be used during the remainder of the Strolll AR intervention for those who are deemed to benefit from it. We will document if AR cues are added to Strolll AR gait-and-balance exercises, and when applicable, specify the type of AR cues as well as their personalized parameters (intercue distance, height, width, audiofeedback, etc.).

To deliver the Strolll AR intervention, participants in this study will by default be equipped with Magic Leap 2 AR glasses for its unmatched vertical AR field of view. Special insert lenses from a complementary lens kit (supports 8 prescriptions from −2.0 to +3.0) made available at each clinical site will be used to correct vision for people wearing spectacles. In case vision cannot be corrected with these insert lenses (e.g., due to a special prescription not part of the lens kit), either tailored insert lenses will be ordered for Magic Leap 2 or Microsoft HoloLens 2 with a slightly smaller vertical AR field of view will be used which can be worn over spectacles to deliver the intervention.

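### Variety in the chosen cue settings does not show that AR cues need personalising, because some settings are fitted to each person by design and no tailored cue is compared with a common one

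*Protocol article*

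**What the plan says.** The secondary objective stands at the end of section 1 (Introduction): "The secondary objective of this study is to evaluate procedures for tailoring assistive AR cues to individuals when deemed beneficial". The expectation attached to it has two parts. Many participants are expected to benefit from cues, and it is expected that "they use a variety of cue settings, thereby substantiating the necessity to personalize AR cues".

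Section 2.2.5 gives the supervised clinic sessions two purposes. The first is "to test the premise that a one-size-fits-all cue does not exist as there is heterogeneity in the effect of cues among participants". The cues kept for the rest of the intervention are those found best for supporting gait, "as evaluated subjectively using both the participant’s experience and the therapist’s impression". On recording, the section states: "We will document if AR cues are added to Strolll AR gait-and-balance exercises, and when applicable, specify the type of AR cues", together with the personalised parameters of those cues.

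The Introduction also describes how settings arise. It starts from the premise itself: "As cueing is not a one-size-fits-all solution (21, 22), the AR cues in the current study will be tailored to the individual’s preferences". Among the gait characteristics to be matched it names "intercue distances fitting a person’s step length and width".

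Section 2.2.7 adds questions to participants at T2 that cover cueing where it was used. Section 2.7 (Statistical analysis) covers group characterisation, feasibility and effectiveness, and names no analysis of cue effects.

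**The concern.** The premise to be tested is about effect: does the same cue help some people and not others? The evidence offered is about settings: do people end up with different ones? These are different quantities, and the procedure links the second to the person whether or not the first is true. Two people with different step lengths receive different intercue distances even if one common distance would serve both equally well.

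At stake is what the trial may conclude on its secondary objective. Read as written, a spread of settings would be reported as showing that personalisation is necessary, and this could shape how the platform is later used. The data described could not carry that conclusion.

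**Working it through.** **Plan's own figure.** The article gives no figure for the cueing objective. Its only power calculation (section 2.4, 29 per group for the TUG) concerns the effectiveness comparison and has no part here.

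**Step 1: set the statements side by side.**
- Premise to be tested (2.2.5): cue effects differ between participants.
- Evidence named (Introduction): settings used differ between participants.
- Source of the settings (Introduction, 2.2.5): matched to gait and preference; best cue judged subjectively.
- Records described (2.2.5, 2.2.7): cue use, type, parameters, and T2 questions on cueing.

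None of the records described sets a tailored cue against a common cue.

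**Step 2: how likely is variety when effects do not differ?** The article gives neither the number of cue types, nor the number of cue users, nor the spread of step length. All three are assumptions below. The upper end of 70 users is the number of completers implied by section 2.4: 100 − 10 − 10 − 10 = 70.

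(a) *Cue type, K equally effective types, m users choosing arbitrarily.* P(at least two types chosen) = 1 − K^(1−m).
- K = 2, m = 10: 1 − 2^(−9) = 0.998.
- K = 2, m = 20: 1 − 2^(−19) = 0.999998.
- For K = 2 to 5 and m = 10 to 70, the lowest value is the 0.998 above.

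(b) *Cue type, one type best for everyone, picked with probability q by subjective judgement.* P(at least one user has another type) = 1 − q^m.

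| q | m = 10 | m = 20 | m = 40 | m = 70 |
|---|---|---|---|---|
| 0.9 | 0.651 | 0.878 | 0.985 | 0.999 |
| 0.8 | 0.893 | 0.989 | >0.999 | >0.999 |
| 0.7 | 0.972 | 0.999 | >0.999 | >0.999 |

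(c) *Intercue distance fitted to step length.* Simulation with an assumed mean of 55 cm, SD of 4 to 12 cm, and settings in 5 cm steps. With 10 users, P(at least two distances) is 0.999 or more. The mean number of distinct distances runs from 3.4 (SD 4 cm, 10 users) to 10.4 (SD 12 cm, 40 users).

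**Step 3: read the results.** For fitted parameters, variety is practically certain whatever the cue effects are. For cue type, some variety is also likely without any difference in effect. The degree of concentration still carries some information: in (b), 70 to 90% of users would be expected on one type, which the records would show. A spread over types, however, also arises in (a), where no cue is better for anyone.

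**The case against.** **The wording is an expectation, and it says substantiating.** This stands. A reader might infer that the article offers variety as proof, or that no result could count against the secondary objective. The text does not support either reading. The objective is to evaluate the tailoring procedures. Low uptake of cues would count against the expectation that many people benefit, and uptake is recorded. Section 2.2.7 also gathers participants' answers on cueing and therapists' experience.

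**Cue type is a within-person choice of what works best.** This stands in part. A reader might infer that the premise cannot fail. That is true in practice for fitted parameters only. Everyone could settle on one cue type, and that would speak against the need to vary it. But the choice is subjective, so a spread of types may equally come from taste or from the therapist's habits.

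**The article does not say that nothing else is recorded.** Correct. Supplements S2 to S4 and the full protocol are not shown and may describe ratings of each cue tried. The point therefore does not rest on missing detail. It rests on the printed inference from variety of settings to necessity, which would remain invalid even if such ratings exist.

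**The calculations rest on assumed inputs, and at least two types is a low bar for variety.** This stands. They show that variety discriminates poorly. They do not show that it is equally probable under every hypothesis.

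**An obvious remedy has its own bias.** If people rate several cues and the best-rated is compared with a default on those same ratings, selection favours the tailored cue. With k equal cues including the default, a non-default cue comes out on top with probability (k − 1)/k: 67% for k = 3 and 80% for k = 5. The remedy below is built to avoid this.

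**Conclusion.** The concern holds in a limited form. The step from a variety of cue settings to a necessity to personalise is invalid for parameters that are fitted by design, and weakly supported for cue type. The statement that the clinic sessions test heterogeneity of cue effect is not backed by any comparison that the article describes.

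The size can only be illustrated. Under the assumed numbers of types, users and step lengths, variety appears with probability 0.998 or more when choice is arbitrary, 0.65 to 0.97 when one type is best for all and there are only 10 users, and 0.999 or more for fitted distances. The finding that variety of fitted parameters is built in needs none of these assumptions.

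This is a minor point on a secondary objective. The TUG comparison, the sample size and the effectiveness analysis are unaffected.

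**What to change.** Limit the secondary objective to describing how many participants use cues and which types and settings are chosen. Delete the inference from variety to necessity in the Introduction, and delete from section 2.2.5 the claim that heterogeneity of cue effect is tested. This costs nothing and remains possible at any stage of recruitment.

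If the claim is to be kept, add a comparison that selection does not bias. After the tailored cue has been selected, each cue user does a fresh trial of that cue and of one fixed default cue (same type and parameters for all), in random order, within the sessions already held. Record participant and therapist ratings from this fresh trial only, and report the paired difference with a 95% confidence interval. The ratings remain subjective and should be described as such.

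The cost is a few extra minutes in the clinic sessions, a short rating line on the session form, and a conclusion that could turn out negative. Recruitment began in May 2024, so the comparison could cover only participants who have not yet passed the clinic phase.

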## Methods and analysis

2

### Study design

2.1

This study is a fully blinded two-armed pragmatic RCT, which will be executed in the Netherlands implemented at multiple physical or exercise therapy clinics. The study consists of three in-clinic assessments performed by participants’ own therapists (Figure 2). After a baseline assessment (T0), participants will start with a 6-week usual care control period, followed by a midterm assessment (T1). Subsequently, participants will undergo 2 weeks of in-clinic familiarization and training with Strolll AR supervised by their therapist. Then, participants will start with the 6-week Strolll AR intervention at home integrated with usual care, followed by the final in-clinic assessment (T2).

**Figure 2 fig2:**
[figure not shown]
Schematic of the study design.

The definition of a pragmatic RCT is that the intervention is tested in a real-world population in a real-world setting (i.e., the clinic), with an appropriate comparison arm (i.e., usual care alone in the current study) and relevant outcomes to determine its effectiveness (24, 25). Special trial designs can be considered. In this particular pragmatic RCT, all participants follow the same T0-control-T1-intervention-T2 procedure, suitable for both between-groups and within-subjects comparisons of the Strolll AR intervention effects as well as for evaluating its clinical feasibility. With regard to the between-groups comparison, participants will be allocated to control (using T0-T1 change data) or intervention (using T1-T2 change data) groups using multiple (*n* = 20) two-armed randomizations following a 1:1 ratio (Figure 3). The randomization will be predefined by an independent person using a Matlab (26) script (see Supplementary material S5), locked with a date and timestamp, and kept concealed from participants, therapists, and researchers. After the final T2 assessment of the last participant, the 20 randomizations of participants over control and intervention groups will be revealed to the researchers and applied in the data analysis (as detailed in section 2.7.3). Participants, therapists, and researchers will therefore all be blind to group allocation during the study, which is impossible for rehabilitation interventions with traditional RCT or cross-over designs. Note that a longitudinal design with a fixed order for all participants may be prone to time-dependent confounding factors, such as progressive worsening of Parkinson’s disease symptoms over time. We would like to emphasize that potential time effects associated with disease progression work conservatively against finding intervention effects. This particular pragmatic RCT design is not recommendable for situations where conditions improve over time (e.g., natural recovery after acute stroke), as this would promote arbitrary intervention effects associated with natural improvement in conditions over time. This design, in which all participants receive the Strolll AR intervention, further allows for a complementary within-subjects evaluation of the intervention effect (i.e., being less susceptible to between-subjects variation than aforementioned between-groups evaluation), while at the same time providing ample information on the clinical feasibility of the Strolll AR platform implemented in the clinical pathway in terms of its safety, adherence, performance, and user experience (i.e., from both participants’ and therapists’ perspectives), making efficient use of scarcely available resources (e.g., funding limiting scientific staff, time limiting availability of clinical staff, patients limiting the number of participants). Moreover, a design with the same procedure for all participants makes implementation of this study in the clinical pathway easier (hence the term pragmatic RCT) and potentially reduces the dropout rate because no participants are withheld from receiving the intervention due to the randomization.

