#### Effectiveness

2.7.3

The effectiveness of Strolll AR for improving TUG, FTSTS, 10MWT, Mini-BESTest, and FES-I will be analyzed according to the per-protocol principle for participants who have completed the final assessment, randomized into control and intervention groups using the 20 concealed randomizations. For each outcome parameter, independent-samples *t*-tests (or their non-parametric equivalents) will be used to compare Control (i.e., using the change scores during the control period; T0-T1) and Intervention groups (i.e., using the change scores during the intervention period; T1-T2). We expect significantly higher change scores for the Intervention group than for the Control group. The 20 predefined concealed randomizations will enable us to perform multiple between-group comparisons, yielding a sensitivity analysis to test the robustness of the effectiveness findings in this pragmatic RCT. That is, this innovative analysis approach will not only provide us with a one-shot indication of the statistical effect, but also with a confidence interval of this effect. Furthermore, multiple randomized comparisons will reduce the likelihood of a systematic confounding effect biasing this pragmatic RCT results, as is often the case when a single one-shot randomization would result in Control and Intervention groups differing significantly at baseline in certain demographic or clinical characteristics. With a multiple-shots randomization, potential effects associated with significant between-group differences in demographics or clinical characteristics of a single randomization will average out over the multiple shots.

As a secondary analysis, which is possible given the design in which all per-protocol participants performed the same T0-control-T1-intervention-T2 procedure, a complementary within-subjects comparison will be performed using repeated-measures ANOVAs with the within-subject factor Time (three levels: T0, T1, T2) for the TUG, FTSTST, 10MWT, Mini-BESTest and FES-I, comparable to the analysis performed in Hardeman et al. (15). For significant main effects of Time, the first and second reverse Helmert contrasts will be used to evaluate Control and Intervention effects, respectively. This will help us interpret (a potential null-finding of) the pragmatic RCT as such a within-subjects comparison is less susceptible to between-subjects variation than a between-groups comparison.

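### The 20 randomisations assign neither treatment nor order, so Strolll AR is confounded with period in every split and averaging over splits cannot remove that

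*Protocol article*

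**What the plan says.** Section 2.1 of the protocol article gives the design label: "This study is a fully blinded two-armed pragmatic RCT". The same section says that "all participants follow the same T0-control-T1-intervention-T2 procedure, suitable for both between-groups and within-subjects comparisons of the Strolll AR intervention effects". On what is randomised, it says that "participants will be allocated to control (using T0-T1 change data) or intervention (using T1-T2 change data) groups using multiple" (20) two-armed splits in a 1:1 ratio. On timing: "After the final T2 assessment of the last participant, the 20 randomizations of participants over control and intervention groups will be revealed" to the researchers, who then apply them in the analysis.

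The periods follow from sections 2.1 and 2.2. T0 to T1 is 6 weeks of usual care. After T1, "participants will undergo 2 weeks of in-clinic familiarization and training with Strolll AR supervised by their therapist", followed by 6 weeks at home and then T2. Section 2.2 gives 14 weeks in total.

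Section 2.7.3 compares the T0-T1 changes of one half with the T1-T2 changes of the other half by independent-samples t-tests, for each of the 20 splits, and states that "multiple randomized comparisons will reduce the likelihood of a systematic confounding effect biasing this pragmatic RCT results". On time effects, section 2.1 concedes that a fixed order is open to time-dependent confounding, argues that "potential time effects associated with disease progression work conservatively against finding intervention effects", and advises against the design where conditions improve over time.

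**The concern.** In a randomised trial, chance decides who receives which treatment, or in which order, and this protects the comparison from confounding with time. Here chance decides only which of two changes, both already measured, is used for each person. Everyone has usual care first and Strolll AR second. Treatment and period are the same variable in every split, and so are treatment and interval length.

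A positive result would nevertheless be reported as the between-group finding of a two-armed RCT, made more robust by 20 randomisations. Readers would credit it with protection against period effects that the design does not give. The Discussion also presents the design as a route to evidence for other technologies, so the label matters beyond this trial.

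**Working it through.** **1. The plan's own figure.** Section 2.4: difference 2.57 s in TUG, SD 3.4 s, d = 0.755, two-sided 5%, 80% power. With the noncentral t distribution, power is 0.792 at 28 per group and 0.807 at 29, so 29 per group and 58 in total are reproduced. The planned losses leave 100 - 10 - 10 - 10 = 70 completers, 35 per group, with power 0.876. The sample-size arithmetic is not at fault.

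**2. What a split estimates.** Score changes so that improvement is positive. Let u be the mean T0-T1 change, t the treatment effect, and b everything else that makes the mean T1-T2 change differ from the mean T0-T1 change.

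- Mean T0-T1 change = u
- Mean T1-T2 change = u + t + b
- Because the split is random, each half represents the whole group, so the expected difference in any split = (u + t + b) - u = t + b
- Expected average of 20 splits = t + b

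The split does not appear in the result. More splits reduce only the noise from who falls in which half.

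**3. Check by simulation.** Assumptions: 70 completers, 20 splits of 35 and 35, zero treatment effect, change SD 3.4 s, correlation between a person's two changes of -0.5, 0 or 0.3, and 2,000 simulated trials per setting. The period effects are illustrative; the documents give none.

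| Assumed period effect (s) | Mean estimate over 20 splits (s) | One split significant at 5% |
|---|---|---|
| 0 | -0.01 to 0.02 | 5% |
| 0.5 | 0.49 to 0.53 | 8 to 10% |
| 1.0 | 0.97 to 1.02 | 21 to 23% |
| 1.5 | 1.50 to 1.51 | 44% |
| 2.57 | 2.57 to 2.62 | 88% |

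The period effect passes through undiminished. The average over splits also correlates 0.95 to 0.99 with the plain within-person difference of the two changes, so it carries almost the same information as an own-control comparison.

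**4. Unequal windows.** T1-T2 is 2 + 6 = 8 weeks; T0-T1 is 6 weeks; 6 + 8 = 14 weeks, as stated. With a steady trend of g per week under usual care and no treatment effect, the expected difference is 8g - 6g = 2g, one third of the usual-care change of 6g. It favours Strolll AR if g is an improvement and control if g is a worsening.

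**5. The planned secondary analysis.** The second reverse Helmert contrast in section 2.7.3 compares T2 with the mean of T0 and T1. Under the same trend it gives 14g - (0 + 6g)/2 = 11g, so it does not remove a steady trend either.

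**6. A contrast that does.** (T2-T1) - (8/6)(T1-T0) = T2 - (7/3)T1 + (4/3)T0. Under the trend: 14g - (7/3)(6g) + 0 = 0. With independent, equal visit errors, its variance is proportional to 1 + 49/9 + 16/9 = 74/9 = 8.22, against 1 + 4 + 1 = 6 for the unscaled (T2-T1) - (T1-T0). The SE ratio is sqrt(8.22/6) = 1.17.

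**The case against.** The design is described openly, and several stronger readings that a reader might infer are not supported.

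- **That the protocol says repeated randomisation removes confounding.** It says only that the likelihood is reduced, and the mechanism it gives is chance baseline imbalance between groups. For that target the statement is right. The fault is that it extends to systematic confounding.
- **That the protocol overlooks time effects.** Section 2.1 gives progression as an example of time-dependent confounding and warns about conditions that improve. What is missing is an argument on direction for anything other than progression.
- **That the other period effects favour Strolll AR.** This cannot be shown. Practice gains that shrink with repetition would favour control, as would regression to the mean after selection at entry. Entry is spread over months from May 2024, so no seasonal direction can be derived. Expectancy is the clearest candidate in favour of Strolll AR, because participants and therapists know which period they are in; an open-label parallel trial would share it.
- **That extra therapist contact is a confounder.** Sections 2.2.5 and 2.2.6 make the clinic sessions and weekly contacts part of the delivered intervention. An 8-week intervention window is legitimate for the same reason; the weakness is the unscaled comparison with 6 weeks.

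It is also true that an own-control analysis is already planned as secondary. It is useful, but it shares the aliasing and, as shown, does not remove a steady trend.

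**Conclusion.** The point holds. Treatment is fully aliased with period and with interval length in all 20 splits, and this follows from the protocol's own description without any numerical assumption. The two-armed RCT label, and the section 2.7.3 sentence where it reaches beyond chance imbalance in person characteristics, claim protection that the design does not have.

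The bias equals the period effect b, whatever the number of splits; unequal windows contribute 2g under a steady trend. Neither b nor g can be sized from the documents, and the net direction is unknown. It would therefore be wrong to conclude that the trial will produce a false-positive result, or that a positive result would be due to period. The conclusion is narrower: the randomisation cannot exclude that explanation. The argument about disease progression covers one mechanism only.

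**What to change.** - In section 2.1 and the abstract, describe the study as a single-group, fixed-sequence (own-control) trial with a usual-care lead-in.
- In section 2.7.3, restrict the confounding sentence to chance imbalance in person characteristics, and state that period effects common to all splits are not removed.
- Limit the effectiveness conclusion to change during Strolll AR relative to the same group's change under usual care. Say that expectancy need not be conservative and that the direction of practice and season effects is uncertain.
- Add, as a sensitivity analysis, the within-person contrast (T2-T1) - (8/6)(T1-T0). Use actual visit dates where they are recorded (the article does not say that they are) and nominal weeks otherwise.

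The cost is a weaker design label, some rewording and one additional analysis. The scaled contrast has about 17% larger SE than the unscaled within-person contrast under independent, equal visit errors. It assumes a linear trend and does nothing about expectancy, season or practice that does not follow one, so it should inform interpretation rather than serve as a pass or fail rule. No visit or participant changes are needed.
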